### Outcomes

#### Primary outcome

The two primary outcomes are: 1) nursing home care staff’s knowledge of ACP and 2) nursing home care staff’s confidence in their own skills regarding ACP (self-efficacy). These outcomes are measured at baseline (T0) and after eight months (T1). We assess knowledge and self-efficacy as these are identified as necessary intermediate steps for healthcare professionals to be able to actually engage in ACP, according to both social cognitive theory and literature about successful ACP [9, 10, 27].

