### Sample size

When we assume unequal cluster sizes with a coefficient of variation of 0.17 and mean size of 30 and an intra-cluster correlation coefficient of 0.036 [30, 31], the design effect for a completely randomised cluster randomised trial is estimated at 2.07, and a sample of 161 staff members for each group across 6 clusters will achieve 80.27% power to detect an effect size of 0.5 at a significance level of 2.5%. This number has been increased to 242 staff members per group (total sample size of 484) to allow for an initial response rate of 70% and a staff turn-over of 10%. Current sample size calculation is valid for a completely randomised RCT (hence assuming a matching correlation of zero and assuming the intervention effect is constant across pairs). To compensate for the loss of degrees of freedom introduced by matching, it is suggested to add two clusters per arm [15].

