#### Analysis

##### Outcome analysis

We will calculate summative scale scores for both primary and secondary outcomes. The resulting scale score for an individual is the sum of the individual item scores. For the knowledge items instructions are provided to check correct answers. If people answered, ‘I don’t know’, this will be scored as an incorrect item. The summative scale score of knowledge is sum correct knowledge items of 11 correct/incorrect answers. The summative scale score of ‘self-efficacy’ is the sum of self-efficacy items on a 10-point scale, ranging from 1 to 10, with 12 items. The primary statistical analyses will use an intention-to-treat (ITT) approach. In ITT the outcome data from all of the samples who were enrolled and randomised to the intervention or control group will be accounted for in the main analyses in the original groups to which they were randomised, regardless of whether or not they completed the ACP+ programme. We will fit a linear mixed model with condition, time and time*condition as fixed factors and with a random intercept for nursing home pair, random slope for time, condition and time*condition at the level of nursing home pair, random intercept for member, random slope for time at the level of member. The need for random slopes will be tested by comparing the difference between − 2 log (max) REML likelihoods with a $$ {\chi}_{1:2}^2 $$ distribution (using a mixture of chi-square distributions). In case of convergence issues, random slopes will also be left out of the model. Estimated cluster-adjusted means with corresponding 95% CI will be reported at T0 and T1, both for the intervention and control group. Differences in mean change (post- measurements minus baseline) between the intervention group and the control group (interaction group*time) will be calculated. All analyses will be two-tailed and considered significant if α = 0.025. Data will be analysed in SAS, R and IBM SPSS.

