This study has several strengths. Firstly, while there are very few high-quality studies that evaluate the effects of ACP in nursing homes, and in particular very few cluster RCTs [3], we contribute to filling this gap by planning and designing this proposed study according to recent recommendations in the conduct of high-quality RCTs [35, 36]. The study design follows that of a previous trial conducted by members of the research team [32]. Therefore, the study protocol has been proved feasible and successful in this study population. Secondly, systematic reviews of ACP highlight that RCTs should be supported by process evaluations that explore implementation issues and identify ‘active elements’ [37] which is an important element of this study. ACP is a complex intervention that ideally targets both organisational and behavioural aspects and is highly influenced by its context (e.g. staffing levels in nursing homes) [17]. Understanding these underlying processes of change can improve our understanding why ACP achieves or fails to achieve intended changes in residents, family or nursing home staff [17]. It can also facilitate the future comparison of similar interventions and the translation to clinical practices or other settings and contexts [17]. We were able to design and plan a process evaluation which is theory-based and structured according to recent guidance [10, 17], enabling us to answer the frequent calls for more transparency in trial results and provide reasons why the intervention did or did not lead to hypothesised effects. As such we will be able to limit something that happened in a recent trial in the Netherlands, where researchers were unable to explain why no effects were found on primary and secondary outcomes [38]. In addition, the results of this process evaluation will enable us to strengthen the links in the theoretical model we have developed in a previous phase [10]. Hence, we will be able to present a theory of how and under what circumstances ACP achieves or fails to achieve desired outcomes. Thirdly, all current trials regarding ACP in nursing homes evaluated outcomes on patient/family level or healthcare use alone (e.g. knowledge of ACP, satisfaction with care, hospitalisation admission rates, number of ADs) [3]. None evaluated the effects of ACP on the level of nursing home staff, while almost all current ACP interventions in nursing homes are educational programmes targeting the knowledge, attitudes or confidence in ACP of professionals [3, 37, 39]. Given that one of the main and most consistently reported factors potentially hindering the completion of ACP is in fact insufficient knowledge of and self-efficacy in ACP among healthcare professionals [8, 40], studying whether and how these educational ACP interventions affect staff outcomes is highly necessary. Considering that a summative evaluation of the effectiveness of our intervention cannot rely on one outcome measure, such as knowledge, we included self-efficacy as primary outcome. Self-efficacy has been identified in social cognitive theory as a mediator for translating knowledge into action (i.e. ACP practices). The results of this trial will be the first to provide evidence of the effects of a complex ACP intervention on staff level outcomes in nursing homes.

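### Testing the two primary outcomes each at a fixed two-sided 0.025 is valid, but Holm's procedure gives more power to show both at the same 5% familywise error

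*Protocol article*

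**What the plan says.** The section on the primary outcome begins: "The two primary outcomes are: 1) nursing home care staff’s knowledge of ACP and 2", the second being care staff's confidence in their own skills (self-efficacy). The Outcome analysis section fixes one threshold for everything: "All analyses will be two-tailed and considered significant if α = 0.025". The Sample size section uses the same level; its 161 staff per group "will achieve 80.27% power to detect an effect size of 0.5 at a significance level of 2.5" per cent.

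The article does not call 0.025 a Bonferroni split and does not state a familywise rate. Both are inferred from two primary outcomes tested at half of 5% each.

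On intervals, Outcome analysis says: "Estimated cluster-adjusted means with corresponding 95% CI will be reported at T0 and T1", for each arm. The tested contrast is the group-by-time difference in change. The text says that this will be calculated and gives no confidence level for it.

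**The concern.** Under the fixed rule each outcome must reach 0.025 whatever the other shows. Holm's rule keeps 0.025 for the smaller p-value and relaxes the second test to 0.05 once the first has succeeded. Strong familywise control at 5% is kept under any dependence between the outcomes, with no added assumption and no added participants.

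The power given up is in showing an effect on both outcomes. That matters here because the Discussion gives this reason for having two: "Considering that a summative evaluation of the effectiveness of our intervention cannot rely on one outcome measure, such as knowledge". Evidence on both outcomes would be more persuasive to the article's readers than evidence on one, and that is where fixed testing loses most.

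**Working it through.** **Inputs from the Sample size section.** "unequal cluster sizes with a coefficient of variation of 0.17 and mean size of 30"; "an intra-cluster correlation coefficient of 0.036"; "the design effect for a completely randomised cluster randomised trial is estimated at 2.07"; 161 per group in 6 clusters; effect size 0.5; level 2.5%. From the Abstract: 14 homes, hence 7 pairs. The correlation between the two test statistics is not given; 0 to 0.7 is assumed.

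**1. Reproduce the stated power.**
- Design effect = 1 + ((1 + CV²)·m − 1)·ICC = 1 + ((1 + 0.0289)·30 − 1)·0.036 = 2.075. With CV² multiplied by 5/6 it is 2.070, as stated.
- Effective size = 161/2.07 = 77.8 per group.
- Noncentrality = 0.5·√(77.8/2) = 3.118, with 2·77.8 − 2 = 153.6 df.
- Power at two-sided 0.025 = 80.26% (stated 80.27%). At two-sided 0.05 it would be 87.3%.

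So the stated power is per outcome at two-sided 0.025, and design and analysis agree.

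**2. Familywise error of the fixed rule.** At most 0.025 + 0.025 = 0.05; if independent, 1 − 0.975² = 4.94%. The rule is valid.

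**3. Holm against fixed 0.025, both true effects 0.5 SD.** Three bases, by simulation:
- A: the article's own power. Normal test statistics with mean 3.093, the value that gives 80.27% at two-sided 0.025.
- B: a matched analysis with 7 − 1 = 6 df, and 161 per group over 7 homes (23 per home). Design effect 1 + (1.0289·23 − 1)·0.036 = 1.816; noncentrality 0.5·√(161/(2·1.816)) = 3.33.
- C: as B but 30 per home (210 per group). Design effect 2.075; noncentrality 0.5·√(210/(2·2.075)) = 3.56.

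| Basis | Correlation | Per outcome, fixed → Holm | Both, fixed → Holm | At least one (either rule) |
|---|---|---|---|---|
| A | 0 | 80.3% → 85.8% | 64.5% → 75.5% | 96.1% |
| A | 0.3 | 80.3% → 85.2% | 67.0% → 76.9% | 93.5% |
| A | 0.5 | 80.3% → 84.8% | 69.1% → 78.2% | 91.5% |
| A | 0.7 | 80.3% → 84.3% | 71.7% → 79.7% | 88.9% |
| B | 0 | 64.9% → 74.2% | 42.1% → 60.6% | 87.7% |
| B | 0.3 | 64.9% → 73.6% | 45.0% → 62.5% | 84.7% |
| B | 0.7 | 64.9% → 72.3% | 51.5% → 66.3% | 78.3% |
| C | 0 | 71.0% → 80.3% | 50.5% → 68.9% | 91.6% |
| C | 0.3 | 71.0% → 79.7% | 53.1% → 70.4% | 89.1% |
| C | 0.7 | 71.0% → 78.2% | 58.7% → 73.1% | 83.3% |

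**4. Where Holm does not help.** With an effect on one outcome only, at correlation 0.3, the power for that outcome moves from 80.3% to about 80.4% (A), 64.9% to 65.2% (B) and 71.0% to 71.3% (C).

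**5. Error under Holm.** With no effect on either outcome, the chance of any rejection is the same under both rules: on basis A, 4.97% at correlation 0 and 4.3% at 0.7; on basis B at 0.3, 4.9%. With a true effect on one outcome only, the false-positive rate on the other rises from 2.5% to about 4.0-4.5% on basis A, still within 5%.

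**The case against.** The strongest reply is that nothing here is wrong. The split is prespecified, controls familywise error, matches the level used to size the trial, and gives the planned 80% per outcome on the article's own basis. It is also simple: a 97.5% interval for the difference in change always agrees with a two-sided 0.025 test. Under Holm that agreement is lost for a second-step rejection with p between 0.025 and 0.05. All of this stands. It is why the point is offered as an improvement and not as a defect.

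It can also be said that the larger gains rest on a 6-df analysis that the article does not commit to, since random slopes may be dropped and no df method is given. That stands too, so the gain on the article's own basis is given first and the 6-df gain is conditional.

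Two stronger readings are tempting and not supported.
- A reader might infer that the 95% intervals contradict a 2.5% test. They belong to single-arm means at T0 and T1, and no decision is read from them. No level is given for the contrast, a detail that an article may leave to the analysis plan.
- A reader might infer from the Discussion that success requires both outcomes to be significant. That sentence explains why self-efficacy was added. No rule requiring both is stated anywhere.

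**Conclusion.** The point holds as a cheap gain in efficiency. The fixed 0.025 rule is valid, and Holm is uniformly at least as powerful at the same 5% familywise error. If both true effects are 0.5 SD and the correlation lies between 0 and 0.7, the chance of showing both rises by about 8 to 11 points on the article's own power basis. It rises by about 14 to 19 points if the matched analysis leaves 6 df. Per-outcome power rises by about 4 to 9 points across these cases.

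The gain depends on both effects being real. The chance of at least one significant outcome is the same under either rule, so the fixed split costs nothing if a single positive outcome is what is wanted. The correlation and the 6 df are assumptions; the remaining inputs are the article's or follow from them.

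**What to change.** In Outcome analysis, for the two primary outcomes only, replace the fixed threshold with Holm's procedure at familywise two-sided 0.05: test the smaller p-value at 0.025 and, if it is significant, test the other at 0.05; otherwise stop. State the 5% familywise rate explicitly. The sample size needs no change, because 0.025 remains the first-step level and the stated per-outcome power becomes a lower bound on its own assumptions. The arm means can keep their 95% intervals.

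The cost is one or two sentences, and the change should be made before unblinded data are seen. The downside is in reporting: if 97.5% intervals are given for the difference in change, a second-step rejection with p between 0.025 and 0.05 will have an interval that includes zero, and needs a footnote to say so.

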##### Analysis of process evaluation data

We will calculate descriptive statistics for quantitative measures (attendance lists, structured diaries, post-training surveys). All qualitative data and transcripts from (group) interviews and focus groups will be analysed using thematic content analysis (via both inductive coding into themes [33] and deductive coding using the theory of change model [10]). The analysis will be carried out by at least two researchers, independently from each other; NVIVO (qualitative data analysis software) will be used for analysis.

### Trial monitoring

The researchers will continuously monitor responses using MS Excel sheets. A Trial Monitor (LP), will be put in place to monitor, together with the research team, the course of the trial. She will act to oversee the progress of the trial and to ensure it will be conducted in accordance with the protocol and GCP [34]. She will also function as main contact person for participating nursing homes to report problems or to ask questions regarding the trial. All data entry will be performed by paid student(s) who are not involved in the research and hired to perform data entry alone. Data will be entered as soon as possible after receipt of each questionnaire in Lime Survey. The Trial Monitor will be responsible for checking and merging trial data. Independent double data entry will be required for 10% of the data to assess accuracy and to avoid data typing or editing errors. We will follow the guidelines of the EMGO’s (Scientific Quality Committee Amsterdam) Quality Handbook regarding data entry accuracy [52]. After data entry, a second database will be created into which a random sample of questionnaires (selected by LP) can be re-entered. The data entry programme identifies double data entry when the second entry is completed correctly. In addition, the researchers (JG or [name]) will check for and delete duplicate data entries after all data have been entered. If the number of errors on any given questionnaire exceeds 3%, the entire questionnaire must be re-entered. With regard to handling missing data, researchers will register the anonymous code (of eligible participants in the primary outcome measurement) for which no survey was received (MS Excel sheet). These codes will be signalled to the contact person who will be asked to send/present a reminder (i.e. the usual questionnaire). If forms have not been returned, up to two reminders are sent out.

### Ethical considerations

#### Potential Harms

The entire team, including an ethicist involved in the research team (CG), is committed to minimize such risks of harm and maximize the benefits for potential participants. However, this study will carry little to no risk to the participating staff and volunteers. Participating staff and volunteers may feel uncomfortable discussing end-of-life care with residents/family and are only included in the training sessions if they are willing to participate. Sensitive and disturbing questions are avoided in the questionnaires and staff may at any point leave a training session or discontinue completing questionnaires, without stating reasons.

Participation in ACP by residents and their family has been considered highly beneficial with little or no burden associated with participation [3]. They may feel uncomfortable discussing questions about quality of life, or end-of-life care preferences about treatment or envisaging themselves as lacking cognitive capacity. Although sensitive and disturbing questions are avoided in the qualitative interviews, it cannot be fully excluded that some people may feel distressed in the process. Participants are free to withdraw their participation from interviews at any stage, and it will be stressed to staff in the training sessions that ACP should be adapted to the individual, considering his/her readiness and willingness to engage in ACP. ACP in this programme is considered a voluntary process for residents and family to engage in.

A series of procedures will be put in place to identify and handle any sign of distress in residents, relatives and nursing home staff/volunteers (e.g. where the participant contacts the researcher): 1) the contact details of the researchers are mentioned on all documents (including training materials for staff/volunteers and leaflets that can be distributed to residents/family) stating they can contact us in cases of distress; 2) if specific concerns arise, the researcher is advised to direct the participant to resources of help if appropriate (e.g. network for palliative care that is available within each region or a support telephone line for both general public and healthcare professionals; http://leif.be/leiflijn/). If we encounter bad practice in a participating nursing home, we will organise a meeting with the research team, followed by the possibility of an informal complaint to the nursing home management, or a formal complaint if this is deemed necessary. In addition, in the process evaluation, we will monitor unanticipated consequences.

#### Anonymity and confidentiality

We ensure anonymity and confidentiality of all participants throughout the study. The involved researchers will never be informed nor be able to be informed of the participating staff’s and volunteer’s identity, or other personal data that can reveal their identity. In each nursing home, a pseudonymising process will take place. Each eligible staff member/volunteer will be assigned an anonymous code, which will enable the research team to link T0 to T1 data. These lists linking names to codes are held by the contact person in the facilities. To have a spare in case the list gets lost, a duplicate will be kept by the Trial Monitor in a sealed envelope located in a locked space. This envelope can only be opened by the contact person in the facility. To preserve the anonymity of the resident and his/her family, no data will be collected from the administrative or medical files. If they agree to participate in interviews or recordings, their names (and nursing home) will be changed when transcribing the recordings. To protect residents’ and relatives’ privacy during the qualitative interviews, nursing home staff, management and volunteers shall be interviewed separately. When interviews are held, a privacy sign will hang at the door.

## Discussion

There is a lack of high quality trials to evaluate the effectiveness of ACP, especially in nursing homes [3]. This cluster randomised controlled trial (RCT), designed to evaluate the effects of the multicomponent theory-based ACP+ programme in Flanders, is unprecedented and will provide important evidence concerning the effectiveness of ACP on nursing home staff and volunteer level outcomes. With accompanying process evaluation, this project will contribute to providing evidence on the effectiveness of ACP in nursing homes and will enable us to provide insights into how and under what circumstances ACP is implemented in nursing homes and hence to develop better implementation strategies.

This study has several strengths. Firstly, while there are very few high-quality studies that evaluate the effects of ACP in nursing homes, and in particular very few cluster RCTs [3], we contribute to filling this gap by planning and designing this proposed study according to recent recommendations in the conduct of high-quality RCTs [35, 36]. The study design follows that of a previous trial conducted by members of the research team [32]. Therefore, the study protocol has been proved feasible and successful in this study population. Secondly, systematic reviews of ACP highlight that RCTs should be supported by process evaluations that explore implementation issues and identify ‘active elements’ [37] which is an important element of this study. ACP is a complex intervention that ideally targets both organisational and behavioural aspects and is highly influenced by its context (e.g. staffing levels in nursing homes) [17]. Understanding these underlying processes of change can improve our understanding why ACP achieves or fails to achieve intended changes in residents, family or nursing home staff [17]. It can also facilitate the future comparison of similar interventions and the translation to clinical practices or other settings and contexts [17]. We were able to design and plan a process evaluation which is theory-based and structured according to recent guidance [10, 17], enabling us to answer the frequent calls for more transparency in trial results and provide reasons why the intervention did or did not lead to hypothesised effects. As such we will be able to limit something that happened in a recent trial in the Netherlands, where researchers were unable to explain why no effects were found on primary and secondary outcomes [38]. In addition, the results of this process evaluation will enable us to strengthen the links in the theoretical model we have developed in a previous phase [10]. Hence, we will be able to present a theory of how and under what circumstances ACP achieves or fails to achieve desired outcomes. Thirdly, all current trials regarding ACP in nursing homes evaluated outcomes on patient/family level or healthcare use alone (e.g. knowledge of ACP, satisfaction with care, hospitalisation admission rates, number of ADs) [3]. None evaluated the effects of ACP on the level of nursing home staff, while almost all current ACP interventions in nursing homes are educational programmes targeting the knowledge, attitudes or confidence in ACP of professionals [3, 37, 39]. Given that one of the main and most consistently reported factors potentially hindering the completion of ACP is in fact insufficient knowledge of and self-efficacy in ACP among healthcare professionals [8, 40], studying whether and how these educational ACP interventions affect staff outcomes is highly necessary. Considering that a summative evaluation of the effectiveness of our intervention cannot rely on one outcome measure, such as knowledge, we included self-efficacy as primary outcome. Self-efficacy has been identified in social cognitive theory as a mediator for translating knowledge into action (i.e. ACP practices). The results of this trial will be the first to provide evidence of the effects of a complex ACP intervention on staff level outcomes in nursing homes.

The study also has some limitations. Firstly, the most important shortcoming is the limited evaluation of outcomes on resident and family level. For several reasons we chose not to include a primary or secondary outcome for the evaluation of effectiveness of ACP+ at resident or family level. Based on previous research [10], we argue improving quality of care, life and dying is beyond the ceiling of accountability (cf. the point at which we stop accepting responsibility for achieving those outcomes solely through the intervention programme), and the likelihood of finding an effect is limited, as was shown in other trials [38]. Because improving staff level outcomes is a necessary precondition before being able to change outcomes for residents and families, we feel this is an important first step in the effectiveness assessment of ACP+. Follow-up funding will enable us to also assess – retrospectively - whether the ACP+ programme had an effect on care concordance at the end of life, based on chart reviews and family interviews of nursing home residents who died during trial period [41, 42], and we will include residents and their families from intervention nursing homes in the process evaluation to evaluate their experiences. We do stipulate that this rationale underlying the study’s aim, generates an additional study limitation, given that changes in staff knowledge/self-efficacy may lead to changes in both behaviour as well resident outcomes. This is an assumption which might have face validity but is not yet supported by evidence about causal inference. We will also not assess economic outcomes simultaneously, which is recommended by recent reviews of ACP effectiveness in older adults [43]. Secondly, because the recruitment follows convenience sampling, there can be systematic differences between those who choose to participate in the ACP+ trial and those who do not. Thirdly, blinding participants (nursing homes and staff) and researchers will not be possible during the study period. During data analysis however, researchers will be blinded. A recent review which used the Oxford Quality Scale to assess methodological trial quality, showed this has not been possible in any of the past trials [43]. This might affect the answers of nursing home staff/volunteers who know they are in an intervention group. Fourthly, we adapted, developed and preliminarily tested a survey to measure knowledge, self-efficacy, attitudes and practices ourselves. However, the self-efficacy scale from Baughman et al., published in 2016, showed high internal consistency and some evidence of convergent, known groups, and predictive validity in family physicians and might be used in the future for similar research, after being tested in this particular population [44]. In addition, responses of staff and volunteers of intervention groups may be affected by their knowledge of their allocation because blinding will not be possible. Finally, because of the high staff turnover in nursing homes it will be unavoidable that throughout the study period of eight months, some staff will change jobs before follow-up data can be collected [45]. This also means that some nursing home staff will not have the possibility to provide baseline data but will be engaged in providing post-assessment at T1.
